9.4 Follow-up of Adverse Events

The Investigator should follow all AEs until occurrence of any of the following:

- AE is relieved or improved to baseline level;
- Investigator confirms no further improvement is expected;
- Subject died;
- Subject lost to follow-up;
- The investigator confirmed that the AE was not related to the study treatment;
- Subject starts a new anticancer therapy;
- No clinical or safety data will be collected, or the database will be finally closed.

The final outcome of each AE, including date of AE resolution or death, must be recorded on the eCRF.

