4.6 Post-exit treatment

The investigator should clearly collect the reasons and time for the withdrawal of subjects, perform the corresponding observation and evaluation for the withdrawn subjects, complete the evaluation content of withdrawal specified in the study plan, fill in the corresponding original records and describe the reasons for withdrawal.

Subjects who discontinue from the study should continue to be followed for adverse events (AEs). These subjects should continue to be followed for AEs, if possible, until they have returned to baseline or the Investigator deems follow-up observation unnecessary. If the adverse event is a chronic condition, the investigator may agree that no further follow-up is required. In this case, the investigator must record his/her opinion in the subject's original medical record and inform the sponsor of the subject's discontinuation as soon as possible.

During the study period, all subjects who receive administration but fail to complete the relevant study contents in the protocol shall be transferred from the last test results to the final results. The investigator should contact the subjects who fail to make return visit as required, and record the contact evidence in the corresponding original records and eCRF (such as: time and date of telephone contact, posting receipt of registered letter, etc.), and properly preserve it.

Subsequent data collection is not required for withdrawals due to:

1) Subject withdraws informed consent;

2) Death of the subject;

3) Study termination by sponsor.

5 Study drug

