9.3 Adverse events of records

During the AE reporting period stipulated in the protocol, the investigator is responsible for collecting all AEs (including SAEs) and recording them in the eCRF. When recording AEs, the investigator should use correct and standardized medical terminology to avoid colloquialisms and abbreviations. The start time of AE, the highest degree of NCI-CTC AE 5.0 grade, the end time, the correlation with the study drug, the influence with the study, the presence or absence of concomitant treatment and the recovery should be recorded.

Diagnosis vs Symptoms and Signs

If a diagnosis is already present, the diagnosis should be recorded in the eCRF rather than individual signs and symptoms (e.g., record liver failure rather than jaundice, elevated transaminases, and flapping tremor). However, if signs and symptoms cannot be attributed to a single diagnosis at the time of reporting, each individual event should be recorded as an AE on the eCRF. If a diagnosis is later established, it should be updated on the eCRF to record the diagnosis.

Adverse Events Secondary to Other Events

In general, AEs secondary to other events (e.g., caused by other events or clinical sequelae) should have their primary event recorded, unless the secondary event is more severe or an SAE. However, secondary events with significant clinical significance should be recorded as independent AEs in eCRF if they occur at a different time from the primary event; if the relationship between the events is unclear, the primary event and secondary event should be recorded separately.

Continuous, intermittent or isolated adverse events (frequency of adverse events)

Continuous AE refers to an AE persisting during the whole process without remission, for example, upper respiratory tract infection lasting for 5 days. Only one AE should be recorded in the eCRF. For severity assessment, the most severe severity throughout the event should be recorded.

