11.5.2 Adverse Events

Adverse event data, after coding according to the current version of MedDRA at the start of coding, were processed in the statistical analysis.

**Treatment Emergent Adverse Events (TEAE): TEAE is defined as an adverse event that appears after or worsens after the use of the study drug.**

Adverse events, treatment-emergent adverse events (TEAEs), Grade 3 and higher TEAEs, serious adverse events, TEAEs related to the study drug, SAEs related to the study drug, TEAEs leading to dose modification, permanent treatment discontinuation, trial discontinuation, and subject death were summarized by number, number, and incidence; adverse events were summarized by SOC and PT; and NCI-CTC AE 5.0 severity grades were calculated by SOC and PT (repeated occurrence of the same AE was analyzed by the most severe number of participants and incidence of severity).

Death, other serious adverse events and adverse events of special interest (AESI). Deaths were defined as all on-study deaths and deaths due to procedures initiated during the study. Other serious adverse events refer to serious adverse events other than death (including SAEs temporally related to or prior to death). AESIs include significant hematological and other laboratory abnormalities (other than those meeting the definition of serious) as well as any event that results in an intervention, including dose reduction, interruption or discontinuation, or significant other concomitant therapy, unless reported as a serious adverse event. The number, number and incidence of the above adverse events and those related to the study drug will be described by SOC and PT. The number, number and incidence of NCI-CTC AE 5.0 will be calculated by SOC and PT, respectively.

A list of subjects with adverse events and a list of subjects with SAEs will be provided.

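### Section 9.4 lets follow-up of an unresolved adverse event stop once it is judged unrelated, which conflicts with the protocol's own rules on final outcome and worst grade

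*Protocol*

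**What the plan says.** Section 9.4 of the protocol sets the rule: "The Investigator should follow all AEs until occurrence of any of the following". Seven conditions follow, and one is enough. The fifth is "The investigator confirmed that the AE was not related to the study treatment" and the sixth is "Subject starts a new anticancer therapy". Neither is qualified by seriousness, grade, whether the event is still ongoing, or whether the patient is still on drug. The section closes with: "The final outcome of each AE, including date of AE resolution or death, must be recorded on the eCRF".

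Other sections bear on the same data:

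- **Section 9.3** says that within the reporting period "the investigator is responsible for collecting all AEs (including SAEs) and recording them in the eCRF", and for a continuous event that "the most severe severity throughout the event should be recorded". Neither depends on cause.
- **Section 4.6** has AEs of discontinued subjects followed, where possible, "until they have returned to baseline or the Investigator deems follow-up observation unnecessary".
- **Section 9.7** requires a report within 24 hours for any serious AE, and then follow-up reports, without regard to relatedness.
- **Section 11.5.2** defines TEAEs without regard to cause. It summarises those of Grade 3 or higher and those leading to death, and counts severity by system organ class and preferred term at the worst grade: "repeated occurrence of the same AE was analyzed by the most severe number of participants and incidence of severity".

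**The concern.** In an uncontrolled trial no comparator arm is available to check causality opinions. Severity tabulated regardless of cause is the safety summary least exposed to them. The fifth condition in section 9.4 brings the opinion back in: once an event is called unrelated, the site need not follow its later course, even if the event is serious or unresolved.

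The protocol itself describes the setting in which this could matter. Section 9.9 says that pneumonitis with this drug class may begin with mild symptoms. The notes to Table 8 ask the investigator to separate it from infectious and other pneumonias. Section 9.10 says knowledge of this drug's AEs is still limited. A lung event first attributed to something else, and worsening afterwards, is a foreseeable case. At stake are the worst grade, end date and outcome of such events, and the attribution of a later death to an AE already closed. A statistical analysis plan cannot repair this, because it cannot recover data that sites were not required to collect.

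**Working it through.** The protocol states no figure on this point, so the check sets its passages side by side.

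**1. What each stop condition in 9.4 does to the record.**

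| Condition | State of the record when follow-up ends |
| --- | --- |
| Relieved or back to baseline; death | Outcome known |
| No further improvement expected | Event stable, outcome can be stated |
| Lost to follow-up; data collection or database closed | Unavoidable end, outcome at last contact |
| New anticancer therapy | Event may be ongoing; later course confounded by the next treatment |
| Judged not related | Event may be ongoing and the patient still seen at visits; collection ends on an opinion about cause |

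Only the last row stops collection because of a view on causality.

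**2. Against the final-outcome sentence of 9.4.** That sentence covers each AE. An event closed as unrelated while ongoing has no final outcome at that moment, and the same section no longer requires anyone to obtain one. The two instructions can be followed together only by entering an unresolved status, which the section does not mention.

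**3. Against 9.3.** Section 9.3 asks for the highest grade over the whole event. The maximum over a shortened observation window can equal the maximum over the full window or fall below it, but cannot exceed it. Any error therefore runs towards lower severity.

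**4. Against 11.5.2.** The incidence of any TEAE depends on onset, which is recorded before any stop condition can apply, so it is unchanged. Summaries that depend on the later course are exposed: Grade 3 and higher, worst grade by system organ class and preferred term, and TEAEs leading to death.

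**5. Against the causality scale.** Section 9.5 (Table 16) has five categories, including one for unlikely and one for definitely unrelated. Section 9.4 does not say which of these triggers the stop. Two of the five criteria (relief after withdrawal or dose reduction, recurrence on re-exposure) need continued observation, so an early stop can remove the evidence that would correct the call.

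**6. Size.** No rate is given. For illustration only, let t be the true share of subjects with a Grade 3 or higher TEAE, u the share of those whose event was called unrelated while still below Grade 3, and w the share of these whose later worsening is not recorded. The observed share is t × (1 − u × w), and the subjects missed among the 80 planned for Stage II number 80 × t × u × w. All three inputs are assumptions.

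- t = 0.40, u = w = 0.10: observed 0.40 × 0.99 = 0.396; missed 80 × 0.40 × 0.01 = 0.3
- t = 0.40, u = w = 0.30: observed 0.40 × 0.91 = 0.364; missed 80 × 0.40 × 0.09 = 2.9
- t = 0.60, u = w = 0.10: observed 0.60 × 0.99 = 0.594; missed 80 × 0.60 × 0.01 = 0.5
- t = 0.60, u = w = 0.30: observed 0.60 × 0.91 = 0.546; missed 80 × 0.60 × 0.09 = 4.3

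The range of 0.3 to 4.3 subjects shows how strongly the answer follows the assumed inputs. It is not an estimate for this trial.

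**The case against.** The best defence is that 9.4 governs follow-up and not collection. Section 9.3 still requires every AE to be recorded at its highest grade. Table 14 runs AE recording from Cycle 1 through the safety follow-up, with visits every 28 days to Cycle 12 and every 56 days after that. Worsening that becomes serious must be reported under 9.7 whatever its cause. A strict reading of Table 16 would also make it hard to call an on-drug infection or lung event definitely unrelated. Much of this stands: on treatment, a good part of the worst-grade data is protected. It does not remove the conflict, because 9.4 gives sites a written release that contains no exception for serious events.

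A reader might infer more than the documents support:

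- **That deaths are lost.** Section 9.3 records a fatal AE as serious, 9.6 covers deaths in the trial or safety reporting period, 11.5.2 tabulates deaths on study, and 12-weekly survival follow-up continues after later therapy. Only the link to an earlier closed AE may be missed.
- **That 4.6 contradicts 9.4.** Section 4.6 leaves discretion to the investigator, which can cover the 9.4 conditions. The wordings differ and should be aligned, but they do not clash outright.
- **That the new-therapy condition has the same fault.** It is not a causality opinion, and grades after a switch are confounded by the next treatment. It is a defensible trade-off.
- **That a final outcome cannot be recorded at all.** An event can be entered as unresolved at last follow-up, and a site may still update it.

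**Conclusion.** The point holds for the not-related condition. As written, section 9.4 allows required follow-up of an unresolved AE, serious or not, to end on a causality judgement. This conflicts with its own final-outcome requirement, with whole-event grading in 9.3 and with the all-cause severity and fatal TEAE summaries in 11.5.2. Worst grade, end date and outcome of some events may be truncated, as may the link from a later death to a closed AE.

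It would go too far to say that all-cause TEAE incidence depends on causality, that deaths go uncounted, or that a planned outcome table is biased; section 11.5.2 plans no such table. The size cannot be derived from the documents. The effect is probably modest, given the visit schedule and serious-AE reporting, and the conclusion rests on the text conflict and not on any assumed rate.

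**What to change.** In section 9.4, remove the not-related condition, so that a causality judgement does not end recording of an AE's grade and outcome. Leave the other stop conditions as they are and add no new cap. Using the end of safety follow-up as a stop, for instance, could shorten follow-up of related events that the present text keeps open. Survival contacts are no substitute for grading: they may be by phone and are described only for survival status and later anti-tumour treatment.

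Then reconcile 9.4 with its own final-outcome sentence and with sections 4.6, 9.3, 9.7 and 11.5.2. State how the outcome of a serious AE still ongoing at the start of new anticancer therapy is entered, for example as not resolved at last follow-up. The change concerns data recording and not patient treatment.

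The cost is an edit to protocol wording and slightly more data entry. A few events may carry a higher final grade in the tables.

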9.5 Criteria for judging the correlation between drugs and adverse events

The investigator should assess the possible association between adverse events and the study drug. See the following 5 criteria for judgment.

1. Whether there is a reasonable sequential relationship between the time of medication initiation and the time of occurrence of adverse reactions;
2. Whether the suspected adverse reactions comply with the types of known adverse reactions of the drug;
3. Whether the suspected adverse reactions can be explained by the effect of concomitant medication, the patient's clinical status or the effect of other therapies;
4. Whether the reaction is relieved or disappeared after drug withdrawal or dose reduction;
5. Whether the same reaction occurs again after re-exposure to the suspected drug.

Table 16 Criteria for determining the correlation between drug and adverse event

|  | 1 | 2 | 3 | 4 | 5 |
| --- | --- | --- | --- | --- | --- |
| Definitely related | + | + | - | + | + |
| Probably related | + | + | - | + | ? |
| Possibly related | + | + | ± | ± | ? |
| Unlikely related | + | - | ± | ± | ? |
| Definitely unrelated | - | - | + | - | - |

Note: + indicates yes, — indicates no, ± indicates difficult to confirm or deny, ? indicates that the situation is unknown

The three items judged as definitely related, probably related, and possibly related to the results were counted as adverse reactions, and the incidence of adverse reactions was calculated accordingly.

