9.8 Unexpected Serious Adverse Events Definitely Related/Suspected to the Study Drug Reaction

Suspected Unexpected Serious Adverse Reactions (SUSARs) that are definitely related/suspected to the study drug during this study should be subject to the Expedited Reporting Standards and Procedures for Safety Data during Clinical Trials issued by the Center for Drug Evaluation on April 27, 2018, which stipulates that the sponsor will perform the expedited reporting of SUSARs during the study, and the investigator is obliged to cooperate with the sponsor in the collection and discussion of relevant data.

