9.10 Adverse Events of Special Interest

TQ-B3525, as an investigational drug, was not exposed to a sample size sufficient to elucidate known adverse events of special interest, and therefore awareness of adverse events associated with this drug remains limited. Potential adverse events that, similar to any new chemical, are generally class-related. Similar PI3K inhibitor drugs have been reported to have hyperglycemia complications, pneumonia/respiratory tract infection, enteritis, rash and other cases. Therefore, throughout the study, investigators should pay special attention to the occurrence and early signs of the above adverse events. In the event of such an event, the investigator should actively discuss with the sponsor representative to confirm the continuation of the event and take active therapeutic measures.

10 Study Data Management

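### Table 16 makes a known reaction type a condition of relatedness, so a drug reaction of a new type cannot enter the adverse-reaction incidence

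*Protocol*

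**What the plan says.** Section 9.5 has the investigator judge each adverse event on five criteria: timing, match to a known reaction type, whether something else explains the event, dechallenge and rechallenge. The second criterion reads "Whether the suspected adverse reactions comply with the types of known adverse reactions of the drug". Table 16 turns the answers into five categories. The text below it sets the counting rule: "The three items judged as definitely related, probably related, and possibly related to the results were counted as adverse reactions". Only these three categories feed the reported incidence. Adverse reactions are part of the secondary safety endpoint in section 2.2.

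Three other places bear on the point:
- Section 9.7 sends every serious adverse event to the sponsor within 24 hours, whatever its causality. The sponsor then assesses both its correlation with the drug and whether it was expected.
- Section 9.8 applies expedited reporting to "Suspected Unexpected Serious Adverse Reactions (SUSARs) that are definitely related/suspected to the study drug during this study".
- Section 9.10 says exposure has been too small to establish the drug's events of special interest, "and therefore awareness of adverse events associated with this drug remains limited".

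**The concern.** Whether a drug caused an event and whether that kind of event was already known are separate questions. Table 16 merges them, because an event must be of a known type before it can be rated even possibly related. For a compound early in development, the reactions the safety objective most needs to find are those not yet on the list, and these are the ones the table excludes.

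At stake is the adverse-reaction incidence in a study whose second stage is meant to support registration. If the summaries of drug-related TEAEs and SAEs in section 11.5.2 use the same three categories, they carry the same bias. The protocol does not say that they do, so this is an assumption. Section 9.4 also allows follow-up of an event to end once the investigator confirms it is unrelated, so a rating lowered by rule may have effects beyond the table.

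**Working it through.** The plan gives no figure to reproduce here. The check is a reading of Table 16 followed by a count.

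**Table 16 as printed** (+ yes, - no, ± hard to confirm or deny, ? unknown)

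| Category | 1 timing | 2 known type | 3 other explanation | 4 dechallenge | 5 rechallenge | Counted |
| --- | --- | --- | --- | --- | --- | --- |
| "Definitely related" | + | **+** | - | + | + | yes |
| "Probably related" | + | **+** | - | + | ? | yes |
| "Possibly related" | + | **+** | ± | ± | ? | yes |
| "Unlikely related" | + | **-** | ± | ± | ? | no |
| unrelated | - | **-** | + | - | - | no |

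The third and fourth rows differ only under criterion 2. That cell alone decides whether such an event counts.

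**Count of patterns.** Criteria 1 and 2 take two values (+, -). Criteria 3 and 4 take three (+, -, ±), and criterion 5 takes three (+, -, ?). This gives 2 × 2 × 3 × 3 × 3 = 108 patterns, 54 for each value of criterion 2. Rows were matched in two ways: strictly (symbols identical) and loosely (± or ? in a row accepts any answer).

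| Criterion 2 | Patterns | Counted, strict | Counted, loose |
| --- | --- | --- | --- |
| + (known type) | 54 | 3 | 27 |
| - (new type) | 54 | 0 | 0 |

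The 27 are those with plausible timing: 1 × 3 × 3 × 3. The 27 matching patterns for a new type all fall in the unlikely row.

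**The clearest case.** Plausible timing, new type, no other explanation, resolution on withdrawal and recurrence on re-exposure give + - - + +. Strictly this matches no row. Loosely it matches only the unlikely row. The same event of a known type (+ + - + +) is definitely related.

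**How easily a type could still be unknown.** This part is illustrative and assumes that the 60 phase I subjects in section 1 are the basis of what is known and that subjects are independent. The chance that a reaction with true incidence p did not appear among them is (1 - p)^60:
- p = 1%: 0.99^60 = 0.547
- p = 2%: 0.98^60 = 0.298
- p = 3%: 0.97^60 = 0.161

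Among the 80 planned stage II subjects such a reaction would be expected in 80 × 0.01 = 0.8, 80 × 0.02 = 1.6 or 80 × 0.03 = 2.4 subjects.

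**The case against.** The strongest objection concerns reach. A reader might infer that a new reaction type drops out of SUSAR reporting. The documents do not support that. Section 9.7 has no causality filter: all serious events go to the sponsor, which judges correlation and expectedness as separate matters. Neither section 9.7 nor 9.8 makes the site's Table 16 rating a gate. What remains is an inconsistency. The protocol's only causality algorithm has no related category for a reaction of unknown type, while sections 9.7 and 9.8 presuppose that a reaction can be both suspected and unexpected. For such an event the site's rating cannot raise the flag, and capture rests on the sponsor.

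A reader might also infer that every unexpected reaction is affected. Criterion 2 concerns type only, so a known type that is unexpected for another reason, such as severity, can still score +.

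Nor are the events lost from the data. Section 11.5.2 tabulates adverse events, TEAEs, grade 3 or higher TEAEs, serious events and events leading to dose changes or discontinuation regardless of causality. Safety is also descriptive, since section 11.2.1 confines inference to the main stage II efficacy measures.

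Three further replies have some force. The table may be meant as guidance: read strictly it leaves most patterns without a row, even for known types, so sites must use judgement. Section 9.10 names class effects, which some sites may treat as known. The phase I probabilities show how a type could be missed, not the bias in an estimate, and the numbers of subjects expected are small.

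All this limits the consequences but does not remove the fault. The sponsor's separate assessment in section 9.7 covers serious events only, and the protocol states no second causality assessment for non-serious ones. If sites depart from the table at their discretion, the incidence depends on which sites do so.

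**Conclusion.** Table 16 is wrong as written and should be fixed. A known reaction type is a necessary condition for every counted category: 0 of 54 patterns with a new type are counted, against 3 (strict) or 27 (loose) of 54 with a known type. For any single new type the adverse-reaction incidence is reported as zero whatever the truth. Across all reactions the bias is downward and probably small in numbers of subjects, but it falls on the events about which least is known.

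This rests on two assumptions: that investigators apply the table as printed and that they do not treat class effects as already known. The extension to drug-related TEAE and SAE summaries assumes that these use the same three categories. The conclusion does not extend to loss of SUSAR reporting or loss of events from the all-causality tables.

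**What to change.** - Let criterion 2 take any value in the definitely, probably and possibly rows.
- Freeing criterion 2 alone would make + - ± ± ? match both the possibly row (counted) and the unlikely row (not counted). Separate the two by criterion 3: unlikely requires + (another explanation accounts for the event), possibly requires ± or -.
- Free criterion 2 in the unlikely row as well. Otherwise a known-type event with an established other explanation (+ + + ± ?) would have no row.
- State that an event is not rated lower only because its type is new, and that expectedness is judged separately under section 9.7. This reconciles section 9.5 with sections 9.7 and 9.8.
- Re-review events rated unlikely solely because of criterion 2.

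On the loose reading, the revised table counts 1 × 2 × 3 × 3 = 18 of 54 patterns for known and new types alike, and the 1 × 1 × 3 × 3 = 9 with another explanation fall under unlikely.

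The cost is an amendment to one table, a notice to sites and re-review of some ratings. The reported adverse-reaction rate will probably rise slightly. Where sites have read ± as accepting any answer, some known-type events with an established other explanation may move out of the count. Design, sample size and treatment are unaffected.
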